### Data assessment

In addition to sociodemographic information (i.e., migration status, socioeconomic status), the school-based screening will cover screening instruments for a broad range of mental health problems. All measures have previously been used in adolescent samples [28–30]. Three self-report instruments will be used to cover help-seeking intentions, actual help-seeking behavior, and attitudes toward help-seeking. The General Help-Seeking Questionnaire (GHSQ [28]) is a self-report measure of help-seeking intentions. Help-seeking intentions for selected mental health problems are assessed on an 8-point scale ranging from 1 (extremely unlikely) to 8 (extremely likely). The Actual Help-Seeking Questionnaire (AHSQ) [31] assesses actual help-seeking behavior by listing potential sources of help and measuring whether or not help has been sought from the respective sources within a specified time period (in the last 12 months; more than 12 months ago). It comprises three sub-scales: whether or not informal help has been sought, whether or not formal help has been sought, and whether no help has been sought. Further, the Inventory of Attitudes Toward Seeking Mental Health Services (IASMHS) [32] will be used. The IASMHS is a 24-item scale and has three internally consistent factors: *psychological openness*, *help-seeking propensity*, and *indifference to stigma*. To assess barriers of help-seeking, 12 items were generated based on a literature review of help-seeking barriers and compared with the validated instrument Barriers to Adolescents Seeking Help Scale (BASH-B [33]). Further, items from the Questionnaire on Social Distance [34], assessing stigma towards peers affected by mental health problems, will be implemented in the screening. Health care utilization of study subjects will be collected by the *Mannheimer Modul Ressourcenverbrauch* (MRV), a scale that lists all possible health care services for a given study sample or risk group and reports the frequency of usage (visits, drug intake, hospital days, etc.) over a given period of time [35]. Similar scales are applied in international cost studies [36]. The MRV was modified and pretested for its use in an adolescent population.

Figure 2 displays an overview of enrollment, interventions, and measures used as well as the corresponding time of assessment. In Additional file 1 a populated Standard Protocol Items: Recommendations for Interventional Trials (SPIRIT) checklist is provided. Additional file 2 provides the World Health Organization Trial Registration Data Set.

**Fig. 2 Fig2:**
[figure not shown]
Schedule of enrollment, interventions, and assessments. *Note:* Monitoring 1: 7 days after registration, Monitoring 2–7: every 14 days for the following 10 weeks, Monitoring 8–14: every 28 days for the following 32 weeks, Monitoring 15: 301 days after registration

Participants receive no direct financial compensation for participating in the school-based assessments. Among all participating C&A, a lottery will be conducted, awarding online gift vouchers (20€ in value) to 5% of the participants.

### Intervention

The intervention is individually delivered via the Internet. All C&A enrolled in this trial receive log-in information to an Internet-based platform that requires secured log-in. The web-based platform contains public content and a personal area with user-specific information and, depending on the group allocation, access to intervention modules. For participants in the control condition, the platform only contains information on the individual results of the school-based assessment and advice to seek professional counseling within the mental health care system. Moreover, the control group is granted access to addresses and names of local mental health care professionals and prompted by a static website encouraging them to seek help at the respective institutions. C&A in the control condition will only be contacted once and are not reminded or followed up outside of the school-based follow-up assessments. The design is justified by testing ProHEAD online against a real-world condition.

C&A allocated to ProHEAD online (intervention group) will receive their individual screening results, individual advice to seek professional help, and contact information for local mental health care professionals. Moreover, the intervention group is granted access to three additional modules: the *Information and Education Module*, the *Motivation and Guided Referral Module*, and the *Monitoring Module*.

#### Information and Education Module

C&A with mental health problems are provided with symptom- and gender-adequate information about mental health problems, personalized to their individual screening profile as assessed within the school-based screening. The module aims at providing tailored psychoeducation to affected C&A in order to reduce the stigma associated with psychopathology and increase mental health literacy. Information on the causes and consequences of mental health problems as well as their prevalence and the possibilities for intervention are provided in a youth-adequate manner. Information was collected and summarized by staff with different occupational backgrounds in consensus with C&A experts in Germany as well as representatives from societies representing patients’ interest. The information was reviewed by a specially invited focus group consisting of C&A between 12 and 14 years with mental health problems. To achieve a broad, comprehensive, and complete *Information and Education Module*, female and male C&A with different diagnoses were invited. These discussions led to revisions of content that weres ultimately implemented in the respective modules.

C&A can access information on all different forms and facets of mental health problems, but specific topics and chapters are highlighted based on their individual needs according to their screening profile in their personal area.

#### Motivation and Guided Referral Module

The *Motivation and Guided Referral Module* provides an important transit between the *Information and Education Module* and actual referral to real-world services. ProHEAD online aims to motivate C&A with mental health problems to seek professional diagnostic assessments and potentially therapeutic help within the conventional face-to-face mental health care systems in manifold ways. Case examples from peers are provided to reduce the stigma and prejudices about seeking and receiving help for mental health problems in order to promote a sense of community among C&A with mental health problems. Further, ProHEAD online offers case management, enabling C&A to chat with trained case managers at youth-adequate times (4 to 10 p.m.) through the ProHEAD online web portal, providing individual guidance and support. C&A are provided with addresses of local authorities and institutions and are offered advice in approaching mental health care services according to their individual needs and preferences. Case managers closely guide and counsel C&A on their way, requesting scheduled updates on individuals’ progress and outcomes. The case managers re-contact C&A via email within defined time frames of disengagement with the web-based platform, to improve binding and gain regular updates on their individual status.

#### Monitoring Module

A monitoring system allows for the gathering of information regarding the help-seeking behavior of C&A in the intervention group. This will enable the case managers to tailor the intervention to a participants´ individual status, situation, and needs, allowing for adequate and tailored support of C&A. We distinguish automatized monitoring from individual monitoring. Automatized monitoring occurs based on user-website interaction in terms of 15 regular online assessments (Monitoring 1: 7 days after registration; Monitoring 2–7: every 14 days for the following 10 weeks; Monitoring 8–14: every 28 days for the following 32 weeks; Monitoring 15: 301 days after registration). As part of the automatized monitoring, C&A receive emails inviting them to complete a short questionnaire and motivating them to stay engaged with the platform. Automatized monitoring ends if C&A report successful help-seeking within the professional mental health care system. Alongside automated prompts, individual monitoring is realized via a team of case managers; each case manager tracks the progress of particular C&A. The case managers have different occupational backgrounds (e.g., psychologist, health education professional) and are trained in motivational interviewing [37] and all study-specific procedures (i.e., administration of the program). Individual monitoring includes individual communication (chat, phone, and email) regarding the progress and status on a regular basis. After registration participants will have access for up to 10 months. The dose of the intervention is primarily determined by the participating C&A. C&A are free to log in to the web-based platform according to their needs and interest. The system will send automated reminders to C&A who stay absent of the platform and have not made efforts to seek conventional face-to-face professional help.

### Outcomes

The primary endpoint of the study is the 1-year follow-up, where all participants will be assessed on mental health problems and help-seeking intentions and behaviors, as well as actual help-seeking within the past year (primary outcome) in a second school-based assessment. A long-term follow-up will take place 2 years after the initial screening. C&A not participating at the school-based follow-up assessment will receive individual notices via email including a link to complete the assessment outside of the school environment if possible. All other medications and treatments used by participating C&A are permitted and will be assessed at the follow-up school-based screenings.

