## Abstract

**Background:**

The highest incidence and prevalence of mental health problems across the lifespan as well as the first onset of most long-term mental health conditions are reported for youths between 14 and 25 years of age. At the same time, only 25% of adolescents with mental health problems receive professional treatment. One explanation for poor treatment access in youths is their low help-seeking behavior. Barriers that can keep children and adolescents (C&A) from seeking professional help include a lack of perceived need, structural barriers, or stigma. Interventions based on e-technology might present an effective approach, overcoming these barriers by reducing stigma and providing low-threshold access with enhanced reach, ultimately facilitating help-seeking for mental health problems among youths.

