**Methods:**

The study is designed as a multi-center, randomized controlled trial. In total, an estimated number of *n* = 1,500 C&A with mental health problems, drawn from a school-based sample of *n* = 15,000 pupils attending school grades 6 to 13 (≥ 12 years of age), recruited in five regions of Germany, will be randomized either to an intervention (ProHEAD online) or a control condition. C&A in the intervention group will receive online access to tailored information and individual advice on where to seek professional help for their specific needs close to their place of living, case reports of and interaction with peers, as well as the opportunity for online and telephone counseling. C&A in the control intervention will receive a recommendation to seek help and online information on where to find professional help. All participants will be asked to complete questionnaires concerning their help-seeking behavior at baseline, during the intervention (monitoring), and also at a 1 and 2 year follow-up. The primary endpoint is the number of C&A seeking conventional face-to-face professional help in the real-world setting within 1 year after their initial screening.

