### Inclusion and exclusion criteria

C&A from the school-based sample (≥ 12 years of age, sufficient German language skills, access to the Internet) are included in the present clinical trial if they endorse any form of mental health problems, including serious suicide thoughts or attempts in the past 2 weeks, a score above 19 points on the Strengths and Difficulties Questionnaire [25] total score, or a score above the defined thresholds for one of its sub-scales: *emotional symptoms* (scores > 6), *conduct problems* (scores > 4), *hyperactivity/inattention* (scores > 6), or *peer relationship problems* (scores > 5). Further, C&A will be included if they report the following: body mass index (BMI) < 5th percentile (adjusted for age and gender) AND concurrent fear of weight gain OR daily binge eating OR daily vomiting OR current alcohol use disorder [26] OR a score above 9 on the Patient Health Questionnaire-9 modified for adolescents (PHQ-A) [27]. C&A scoring below all clinical cut-offs are allocated to other trials nested within the ProHEAD Consortium. C&A not providing written informed consent (including parental consent) will be excluded.

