### Sample size

Based on the expected sample size to be allocated by randomization (*n* = 1,500), a power analysis for the trial revealed that the study is powered to detect small effects (1.13 ratio, i.e., 13% differences in help-seeking between groups, alpha = 5%), assuming a critical χ^2^ = 34.55. All tests will be two-sided.

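### Pupils already in professional care can count as primary-outcome events in both arms, and the primary test does not adjust for baseline care: power is lost, without bias between arms.

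*Protocol article*

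**What the plan says.** All references are to the protocol article.

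- **Inclusion and exclusion criteria.** Entry rests on symptom thresholds. The only exclusion given is "C&A not providing written informed consent (including parental consent) will be excluded". Current or past treatment is not mentioned.
- **Outcomes.** The primary outcome is "actual help-seeking within the past year (primary outcome) in a second school-based assessment". The same section permits all other treatments.
- **Abstract (Methods) and Hypotheses.** The help that counts is formal face-to-face care, in the Hypotheses from a child and adolescent psychiatrist or psychotherapist. The Abstract sets the window as "within 1 year after their initial screening". Neither place limits the outcome to a first or new contact.
- **Statistical analysis.** The primary comparison is a chi-squared or Fisher test of users against non-users of professional help. Missing outcomes count as no help. The only adjustment mentioned is for class and school, if needed. Earlier care is not among the predictors listed for the secondary regression.
- **Data assessment.** The help-seeking questionnaire (AHSQ) asks about sources of help "within a specified time period (in the last 12 months; more than 12 months ago". A resource-use questionnaire (MRV) is also collected. The Abstract states that help-seeking is asked at baseline.
- **Abstract (Background).** The text says that "only 25% of adolescents with mental health problems receive professional treatment"; the Background section repeats the figure.

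**The concern.** The intervention is meant to bring pupils into care: its modules motivate, guide referral and stop automated monitoring once professional help has been found. A pupil who is already in care has little left to gain on this outcome, yet is scored the same as one newly brought in.

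Such pupils add events to both arms that do not respond to the intervention. The difference between arms shrinks in proportion to their share, and the ratio moves towards 1. At stake is the chance of detecting a modest real effect, and a clear reading of the result: the overall percentages would mix continuing care with newly started care.

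**Working it through.** **Inputs.** From the article: 1,500 randomised, two-sided 5% test. The allocation ratio is not stated; I assume 1:1, so 750 per arm. Assumed, because the article gives no values: the share in care at screening f (25% taken from the background figure, with 15% and 33% as a range); the proportion s of those pupils who report care again at one year; and new uptake of 20% (control) and 27% (intervention) among the rest.

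**The plan's own power statement.** It gives a 1.13 ratio, glossed as "i.e., 13% differences in help-seeking between groups, alpha = 5", and a test "assuming a critical χ^2^ = 34.55". It states no control rate, power or degrees of freedom, and it does not reproduce. The 5% critical value for a 2×2 table is 3.84. With 750 per arm a ratio of 1.13 has 23% power at a 20% control rate and reaches 80% only near a 55% control rate. A 13-point difference has more than 99.9% power at control rates from 10% to 60%. That is a separate matter. It matters here because the plan fixes no single target effect, so both small and large effects must be shown.

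**Dilution, s = 100%.** Observed rate = f + (1 − f) × new uptake.

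- Control: 0.25 + 0.75 × 0.20 = 0.400
- Intervention: 0.25 + 0.75 × 0.27 = 0.4525
- Difference 5.25 points instead of 7; ratio 1.13 instead of 1.35

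Power = Φ[(d − 1.96 × SE0) / SE1]:

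- pooled rate 0.42625, SE0 = √(0.42625 × 0.57375 × 2/750) = 0.02554
- SE1 = √((0.400 × 0.600 + 0.4525 × 0.5475)/750) = 0.02550
- (0.0525 − 1.96 × 0.02554)/0.02550 = 0.096, so power is 54%

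| Share in care | Control | Intervention | Power, planned test |
|---|---|---|---|
| 0% | 20.0% | 27.0% | 89% |
| 15% | 32.0% | 38.0% | 68% |
| 25% | 40.0% | 45.3% | 54% |
| 33% | 46.4% | 51.1% | 44% |

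**A large effect.** With 20% against 33% among pupils not in care and f = 25%, the observed rates are 40.0% and 49.75%. SE0 = 0.02568, SE1 = 0.02556, and (0.0975 − 1.96 × 0.02568)/0.02556 = 1.85, so power is 97%.

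**Effect of adjustment, f = 25%, all 1,500 kept.** Observed rate = f × s + (1 − f) × new uptake; adjusted power by simulation.

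| s | Control | Intervention | Unadjusted | Adjusted |
|---|---|---|---|---|
| 90% | 37.5% | 42.75% | 54% | about 73% |
| 70% | 32.5% | 37.75% | 56% | about 64% |
| 50% | 27.5% | 32.75% | 60% | about 62% |

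The closed formula gives 55%, 57% and 60% for the unadjusted column. I repeated the simulation with a Mantel-Haenszel test and with logistic regression; both agreed with the adjusted column to within about one point. The simulation takes baseline care as correctly reported.

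**Recall window.** The AHSQ categories count back from the day of completion, while the endpoint counts forward from screening. The two coincide only if follow-up falls at 12 months. The Outcomes section lets pupils who miss the school session answer by an e-mailed link, and states no time limit.

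**The case against.** The strongest reply is that nothing here is invalid. Care at screening precedes randomisation, so it is balanced in expectation, and the type I error is unaffected. Total use of professional care among all randomised pupils is a coherent pragmatic endpoint, stated consistently in the Hypotheses and the Statistical analysis. This stands: preferring new contacts is a choice of estimand.

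The size is also open to challenge. The 20% and 27% are not from the article, and a 13-point effect would survive dilution. Existing patients count only if care continues or recurs and follow-up is completed, since missing outcomes count as no help. This stands too, and is why the ranges are shown.

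Three stronger readings are tempting and are not supported:

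- **That a quarter of this trial's participants are in care.** The 25% describes adolescents with mental health problems in general. The trial's own share is unknown.
- **That the primary analysis should be restricted to pupils not in care.** Under the same assumptions that set (562 per arm, 20% against 27%) has 79% power. But it changes the estimand, and the AHSQ as described does not identify current care. Restricting on it would also drop pupils whose care had ended, for whom re-entry could be a real effect of the intervention.
- **That the recall item miscounts specific months.** The article schedules the repeat survey at 12 months and gives no visit window, so any early or late date would be invented.

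What remains is that a strong candidate predictor of the outcome is collected before randomisation and left unused in the primary test.

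**Conclusion.** The point holds as a loss of efficiency. Continuing patients are eligible, can count as events in either arm, and are not accounted for in the primary test. It should not be read as bias between arms or as a flaw that invalidates the trial.

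The size depends on three unknowns: the share in care, how many of them report care again, and the true effect. For an assumed 7-point effect with everyone in care reporting it again, planned power is 68%, 54% or 44% at 15%, 25% or 33% in care. For a 13-point effect at 25% in care it stays at about 97%. The gain from adjustment is large when care persists and almost nil when half of those in care report none a year later. A criterion shown only in the trial-flow figure, which was not available, cannot be ruled out.

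**What to change.** 1. Keep all randomised pupils in the primary analysis, and stratify or adjust the primary test for professional help-seeking reported at baseline (AHSQ or MRV), for example by a Mantel-Haenszel test or logistic regression. Name the baseline item and its coding before outcome data are seen.
2. Prespecify, as a supporting analysis, new professional contact among pupils who reported no professional care at baseline.
3. Restate the power calculation with an assumed control rate, share in care and persistence.
4. As a minor wording point, anchor the follow-up help-seeking item to the first school survey, so that it matches a window defined as "within 1 year after their initial screening".

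The cost is analysis wording and one reworded item. No extra pupils, visits or instruments are needed, and the intention-to-treat set is unchanged. An adjusted odds ratio is conditional on baseline care, so the overall percentages by arm should be reported beside it.

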### Statistical analysis

The main hypothesis is that a greater proportion of those C&A with mental health problems who are randomized to ProHEAD online (intention-to-treat) will present themselves within the conventional professional mental health care system after 1 year compared to C&A in the control condition. This will be addressed using chi-squared tests with Fisher’s exact *F* to adjust for zero inflation of cell distribution sizes (C&A who utilized professional help versus C&A who did not utilize professional help) on group differences. In secondary analyses, predictors of help-seeking behavior (i.e., sex, age, utilization of the online intervention, and symptom severity at initial school-based screening) will be assessed using multinomial logistic regression analyses. Engagement time per participant (minutes per day, days per month) and content of engagement will be tracked to get a reliable estimate of the utilization of the platform that is of interest for analyses of the dose-response relationship. Missing data and subjects withdrawn from the trial will be handled using an intention-to-treat approach. All subjects randomized will be considered in the analyses. In the case of drop-outs or missing data, it will be assumed that these C&A did not present themselves within the mental health care system to provide a conservative estimate of the true effect. Potential class and school effects will be tested and adjusted for if necessary.

In addition, a cost-effectiveness analysis, including the calculation of the incremental cost-effectiveness ratio (ICER), will be conducted. To provide information on cost per quality-adjusted life year (QALY), cost-utility analyses will be used.

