## Hypotheses

The primary hypothesis is that a greater proportion of C&A with mental health problems who are randomized (intention-to-treat) to help-seeking assistance through an individualized online based intervention are more likely to actually utilize professional (formal) face-to-face mental health care from a child and adolescent psychiatrist or psychotherapist within 1 year (primary endpoint), compared to a control group receiving information only. Secondary hypotheses are that C&A allocated to the intervention group will score more favorably on measures of mental health problems, health-risk behaviors, and quality of life in the respective follow-up assessments, compared to the control group. Additionally, health economic analyses will be conducted to assess economic aspects of the newly developed intervention.

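### The primary comparison uses no baseline predictor of help-seeking although likely ones are collected before randomisation; the test is valid but gives up precision that would cost only wording to recover

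*Protocol article*

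**What the plan says.** On the primary hypothesis, the Statistical analysis section states: "This will be addressed using chi-squared tests", with a Fisher exact variant. The table is professional help used or not used, by arm.

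Individual characteristics appear only afterwards: "In secondary analyses, predictors of help-seeking behavior (i.e., sex, age, utilization of the online intervention, and symptom severity at initial school-based screening". One of these four, utilization of the intervention, arises after randomisation. The one adjustment that could reach the primary comparison is conditional and concerns clustering: "Potential class and school effects will be tested and adjusted for if necessary".

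The baseline information exists. The abstract says: "All participants will be asked to complete questionnaires concerning their help-seeking behavior at baseline". The Data assessment section adds: "Three self-report instruments will be used to cover help-seeking intentions, actual help-seeking behavior, and attitudes toward help-seeking". These are the AHSQ (actual help-seeking, split into the last 12 months and earlier, with formal help as a sub-scale), the GHSQ (intentions) and the IASMHS (attitudes). Under Randomization and blinding, allocation follows the school screening, so these values precede allocation.

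**The concern.** The primary outcome is actual help-seeking over the past year. The baseline AHSQ asks about the same behaviour over the year before, so it is close to an earlier reading of the outcome. Prior treatment is not listed as an exclusion, and other treatments are permitted, so pupils already in contact with services can be randomised. Severity at entry can vary widely, from one SDQ sub-scale above its threshold to a recent suicide attempt. It is therefore plausible that baseline values predict who will report help a year later.

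A test of two proportions leaves all of that variation in the standard error. Adjusting for baseline variables in a randomised comparison removes the explained part at no cost in validity. What is at stake is a wider interval and lower power than the trial's own data allow.

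The secondary predictor analysis does not fill the gap. It is not presented as the test of the treatment effect, and because it includes utilization it cannot serve as an adjusted estimate of that effect.

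**Working it through.** **The plan's own figure.** The article gives no precision figure, R2 or correlation to reproduce. The nearest statement is in the Sample size section: n = 1,500, a ratio of 1.13 described as a 13% difference, alpha 5%, critical chi-squared 34.55. It could not be reproduced: the 5% critical value on 1 degree of freedom is 3.84, and neither a power level nor a control rate is stated. That is a separate matter. Here it means that the lost precision cannot be tied to a planned power.

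**Inputs.** N = 1,500 (Sample size). Assumed: 1:1 allocation, so 750 per arm; control rate 25%, borrowed from the share of adolescents treated in the Background; R2, varied; 30% missing outcomes, used as an example.

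**Step 1: gain without missing outcomes.** Adjustment multiplies the variance by about (1−R2), so the equivalent sample size is N/(1−R2).

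**Step 2: effect of counting missing as no help.** Suppose a share m is missing, unrelated to baseline or outcome. With p the true rate, the explained variance falls to (1−m)²·R2·p(1−p), and the total variance of the analysed outcome is (1−m)p·[1−(1−m)p]. For m = 0.30 and p = 0.25, the diluted R2 is R2 × 0.49 × 0.1875 / (0.175 × 0.825) = 0.636 × R2.

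| R2 (assumed) | 1,500/(1−R2) | Gain, none missing | Gain, 30% missing |
|---|---|---|---|
| 0.02 | 1,531 | 2.0% | 1.3% |
| 0.05 | 1,579 | 5.3% | 3.3% |
| 0.10 | 1,667 | 11.1% | 6.8% |
| 0.15 | 1,765 | 17.6% | 10.6% |
| 0.25 | 2,000 | 33.3% | 18.9% |

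Read backwards, a 10% gain needs R2 = 1 − 1/1.10 = 0.091, and a 35% gain needs 1 − 1/1.35 = 0.259. With 30% missing these become 0.058 and 0.165, or gains of about 6% and 20%.

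**Step 3: how strong the predictors must be.** At a 25% rate with nothing missing, a 10% gain needs a baseline AUC of about 0.69 and a 35% gain about 0.82. An AUC of 0.57–0.63 yields only 1–5%.

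**Step 4: illustration with one covariate (all values assumed).** Let 25% of pupils have earlier help, with 1-year rates of 60% among them and 15% in the rest. The overall rate is 0.2625, and R2 = 0.25 × 0.75 × 0.45² / (0.2625 × 0.7375) = 0.196, a gain of 24.4%. With 30% missing, R2 is 0.124 and the gain 14.2%.

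**Step 5: consequence for the effect.** At a 25% control rate, the difference detectable with 80% power falls from 6.5 points to 6.2 (R2 0.091) or 5.6 (R2 0.259). For the stated ratio of 1.13, power moves from 29.6% to 32.0% or 38.0%. If the stated 13% means 13 points, power already exceeds 99.9% and adjustment adds almost nothing.

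**Step 6: validity and check by simulation.** With 750 per arm, a 25% control rate, no missing outcomes and R2 of 0.10, 0.17 and 0.26, a standardised adjusted risk difference had variance 0.89, 0.82 and 0.73 times the unadjusted one, in line with (1−R2). Its type I error was 4.8–5.3%. The unadjusted test had 4.8%.

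**The case against.** The strongest reply is that nothing here is wrong. A test of two proportions in an individually randomised trial of 1,500 is valid, prespecified and answers the hypothesis as posed. Chance imbalance in a predictor is already covered by its error rate. This stands in full: the point concerns efficiency only.

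A second reply is that no one knows how well these variables predict. This also stands. A reader might infer that the predictors are strong and that the trial throws away the equivalent of 10–35% more pupils. The document does not support that. It says the listed variables will be examined as predictors, gives no measure of association, and sets a missing-data rule that dilutes whatever association there is.

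A reader might also take the secondary hypothesis, that the intervention group "will score more favorably on measures of mental health problems, health-risk behaviors, and quality of life in the respective follow-up assessments", as a plan to compare follow-up scores without the screening value. It is a hypothesis, not a model. The article fixes no analysis for the score outcomes, so there is nothing to criticise there. Likewise, the remark about a conservative estimate of the true effect justifies the rule for missing data. It does not describe what the chi-squared test delivers.

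A last reply is that covariates are a matter for the analysis plan. That would hold had the article left the primary method open, but it names the test and places individual predictors in secondary analyses.

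**Conclusion.** The point holds as an improvement that costs nothing, not as an error. The primary comparison as written uses no prognostic baseline value. The conditional class and school adjustment does not change this, and the secondary predictor model is no substitute. The precision given up is unknown: about 1–5% more pupils for weak predictors, 11% at R2 0.10 and 33% at R2 0.25, and less once missing outcomes count as no help. These figures rest on an assumed R2; the AUC, dilution and power figures also assume a 25% rate, the power figures assume equal arms, and the dilution assumes 30% missing at random. Confidence is high that covariates are absent, and low for any single percentage. Adjustment would not repair the Sample size statement, which needs its own correction.

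**What to change.** Name as the primary result a covariate-adjusted risk difference with 95% confidence interval and p-value. Obtain it by standardisation from a logistic model with arm and a fixed list of baseline covariates: prior formal help-seeking (AHSQ), help-seeking intention (GHSQ), symptom severity on one named scale, age, sex and region. Use robust standard errors. State that no variable arising after randomisation, platform utilization in particular, enters this model. Keep the chi-squared or Fisher test as a supportive analysis. The rules for missing outcomes and for class and school effects are not altered by this change.

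The cost is wording in the Statistical analysis section, with no new data, visits or pupils. The covariate list must be fixed before outcome data are seen, because choosing covariates afterwards would undermine the result.
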